##### Daily self-report

1.4.2.1

In the morning and evening assessments, well-being (mood, tension, exhaustion, rumination) and sleep in the previous night are assessed. In the evenings, daily self-reported depressive symptom severity is assessed using the Patient Health Questionnaire-2 (PHQ-2 [43]), a very short measure assessing two core symptoms of depression (loss of interest/joylessness and feeling down/depressed/hopeless). Following previously established procedures [15,16], answers are given on a Visual Analogue Scale ranging from 0 to 10 with labelled endpoints (0 = never, 10 = all the time). Additionally, contextual information is queried to facilitate the interpretation of the data (substance use, medication, daytime activities).

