##### Weekly self-report

1.4.2.2

The Patient Health Questionnaire-9 (PHQ-9, [44]) is used to assess the weekly self-reported depressive symptom severity. To this end, the original wording of the introductory sentence was changed to “Over the *last week*, how often have you been bothered by any of the following problems?“. The PHQ-9 is a short self-report measure of depressive symptoms that is able to detect changes in depression over time [45] and has been recommended as a general measure of depression severity by the DSM-5 [39]. Each item is rated on a four-point Likert scale ranging from 0 to 3, total scores range from 0 to 27. Higher scores indicate more severe depressive symptoms.

The Situational Self-Awareness Scale (SSAS, [46]) is used to assess weekly fluctuations in public and private self-awareness occurring at the time of self-monitoring during this study. Data can be used to clarify the relation between self-awareness, continuous self-monitoring, and depressive symptoms. The SSAS is sensitive to changes in self-awareness within individuals over time and across situations [46]. A German version is used which was created by two native German speakers using the double-translation and reconciliation procedure [47].

Additionally, participants are asked weekly about life events (“Were there any special events this week that concern you?“), with the option to enter a free text note in the iTD-App.

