### Data analysis

1.6

The current study does not encompass confirmatory hypothesis testing and has explorative character, aiming to provide proof-of-concept for the value of personalized monitoring and forecasting of depression severity in individual patients. Missing data will be handled with model-specific imputation when needed.

To answer RQI, i.e. “Can personal MS data be an objective marker of the a) daily and b) weekly self-reported depressive symptom severity?“, we will conduct multilevel correlations between depressive symptom severity (PHQ-2, PHQ-9) and features derived from MS data through the application of data-driven methods. Multilevel approaches can be applied for statistical analyses of idiographic data [49,50]. Multilevel correlations will include participants as fixed effects and as random effect. All MS features will be included in the mixed model as fixed effects. However, in multilevel models, within-person variability is pooled across individuals, rather than person-specific [51]. Therefore, we will repeat analysis for each participant separately (truly idiographic *N* = 1 version of the analysis) to understand whether there are any differences in results if the data base is limited to MS features derived from personal data of the individual only. Apart from the correlations themselves, the effect sizes will be assessed to understand the clinical relevance of associations and a Random Forest classifier will be used to account for non-linear associations and to asses feature importance using Kernel SHAP analysis [52]. To validate our findings on an idiographic level, we will explore the use of unified structural equation modelling (USEM, [53,54]), including Group Iterative Multiple Model Estimation (GIMME; [55,56]) that can estimate both group-level relationships and individual-specific relationships.

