To address RQII, i.e. “Can personal MS data predict the self-reported depressive symptom severity on a) the next day(s) and/or b) the next week(s)?“, we apply various machine learning techniques. Exploratory analyses investigate the predictability of depressive symptoms within individuals, using either classification or regression approaches. We compare idiographic models, which use data from individual patients, with nomothetic models based on data from all participants. Furthermore, we plan to examine whether multitask-learning methods [57] can enhance performance. Modern machine learning models, such as deep neural networks (DNNs), are validated against classical state-of-the-art methods, including boosted ensemble techniques [58], support vector machines [59], and autoregressive models [32] focusing on vector autoregressive (VAR) models and their analyses using forecast error variance decomposition (FEVD) and impulse response functions (IRF) specifically for idiographic approaches. Individual thresholds for high depressive symptom severity are derived from the data. Using eXplainable AI (XAI) methods, we evaluate the sensor technology component within iTD to understand the significance and impact of various MS features on the model's outcomes. This will help to identify the most relevant aspects of the MS data and clarify their influence on potential decision-making processes. Models based on data from all participants are validated using leave-one-subject-out cross-validation (LOSO-CV) [60,61], while within-subject models employ time-series cross-validation [62,63] and rolling back cross-validation [64].

For both RQ, sensitivity analyses will be conducted using different amounts of input data (e.g., 12 vs. 24 h of MS data, all AA vs. only MS data).

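### RQI's only named non-linear analysis is a Random Forest classifier, although PHQ-2 and PHQ-9 are graded scores; the check and its SHAP ranking therefore address a coarser outcome than the correlations they supplement

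*Protocol article*

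**What the plan says.** All statements are in the protocol article.

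- **Main RQI analysis (section 1.6, Data analysis):** "we will conduct multilevel correlations between depressive symptom severity (PHQ-2, PHQ-9) and features derived from MS data". The analysis is then repeated for each participant separately. No cutting of the scores is mentioned.
- **Non-linear supplement (same section):** "a Random Forest classifier will be used to account for non-linear associations". The same model is to "asses feature importance using Kernel SHAP analysis". Within RQI no other method is named for non-linear associations, and no number or position of classes is given.
- **Daily outcome (section 1.4.2.1):** for the two PHQ-2 symptoms, "answers are given on a Visual Analogue Scale ranging from 0 to 10 with labelled endpoints".
- **Weekly outcome (section 1.4.2.2):** for the PHQ-9, "Each item is rated on a four-point Likert scale ranging from 0 to 3, total scores range from 0 to 27".
- **Contrast with RQII (section 1.6):** symptoms are to be predicted "using either classification or regression approaches", and "Individual thresholds for high depressive symptom severity are derived from the data". Both statements stand in the RQII paragraph only.

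**The concern.** RQI asks whether sensed behaviour and physiology are associated with severity, and severity is measured on graded scales. The correlations address that question. The forest is there to catch what correlations miss because they are linear, and to say which features matter.

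A classifier predicts class membership, so two things change at once between the correlations and the forest: the learner (linear to non-linear) and the outcome (graded to classed). If a feature ranks high in the SHAP analysis but shows little correlation, or the reverse, non-linearity is one explanation and the changed outcome is another. The plan offers no way to separate them. Cutting the scores also discards information, which matters most for the weekly PHQ-9, with only about 52 values per person.

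The word is unlikely to be loose usage for any forest, because the next paragraph separates classification from regression. The model type is stated and does not match the outcome, so this is more than a detail left to a fuller plan.

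**Working it through.** The article gives no information, power or sample-size figure for this analysis, so there is none to reproduce. Two checks apply.

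**1. What a classifier can do with these scores**

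There are two options.

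- *Cut the score into a few classes.* Differences within a class are discarded.
- *Use every score value as its own class.* A standard classifier ignores the order of the classes. The PHQ-9 total can take 28 values (0 to 27). One year gives about 52 weekly scores per person, so on average 52/28 = 1.9 observations per value.

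Under either option the target is no longer the graded severity used in the correlations.

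**2. Size of the loss if the score is cut**

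Inputs from the article: 365 days of follow-up per person (section 1.1), so at most about 365 daily and 52 weekly scores.

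Assumptions, because the article does not give them: the score is roughly normal, and the number and place of the cuts are varied.

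Formula: the share of the variance of a standard normal score Y that is kept after cutting is the sum over classes of (φ(a) − φ(b))² / p, where a and b are the class limits and p is the class share. With two classes and a share q in the upper class, this is φ(z)² / [q(1 − q)], with z the cut-point.

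| Classes | Calculation | Kept | Lost |
|---|---|---|---|
| 50/50 | 0.3989² / 0.25 | 0.637 | 36% |
| 75/25 | 0.3178² / 0.1875 | 0.539 | 46% |
| 80/20 | 0.2800² / 0.16 | 0.490 | 51% |
| 90/10 | 0.1755² / 0.09 | 0.342 | 66% |
| 3 equal | 2 × 0.3636² / (1/3) | 0.793 | 21% |
| 4 equal | general formula | 0.861 | 14% |
| 5 equal | general formula | 0.897 | 10% |
| 10 equal | general formula | 0.959 | 4% |

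Sensitivity to the normal assumption, two classes from 50/50 to 80/20: the loss is 25% to 52% for a uniform score and 35% to 52% for an exponential score.

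A regression forest on the uncut score has no such loss, by construction.

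**The case against.** The strongest case on the other side has five parts.

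- **The size of the loss is not fixed by the document.** A reader might infer that a third to a half of the information is lost outright. The article does not support that. It gives no classes for RQI, and its only threshold text concerns RQII. The range needs a two-class cut between 50/50 and 80/20. With more classes the loss is much smaller. This objection stands.
- **The formula is for a linear association.** A reader might convert the shares into counts (365 × 0.637 = 232 down to 365 × 0.490 = 179 daily scores; 52 × 0.637 = 33 down to 52 × 0.490 = 25 weekly scores). These are not effective sample sizes for a forest chosen because associations may be non-linear. The percentages are a guide only. This also stands.
- **Validation.** A reader might infer that the SHAP values will come from a forest never tested on held-out data. Section 1.6 does not say so. Its cross-validation schemes stand in the RQII paragraph but are worded by model type, and such detail for one supplementary model is commonly left to a fuller plan. No error is shown here.
- **Classification is a legitimate exploratory question, and no formal comparison of forest and correlations is planned.** Both are true. But the forest is introduced to account for non-linear associations with severity. It supplements the correlations, and readers will set the two side by side. A class outcome answers an additional question and leaves the one about severity open.
- **The consequence is small.** The multilevel and single-person correlations show no sign of cut scores, RQI also explores structural equation models, and RQII allows regression. This limits the weight of the point without removing it: within RQI, the forest remains the only method named for non-linear associations and the source of the SHAP ranking.

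**Conclusion.** The point holds as a mismatch between a stated method and its outcome. RQI's non-linear check and Kernel SHAP ranking rest on a classifier, while PHQ-2 and PHQ-9 are graded. Whether the scores are cut or their values are used as unordered classes, grading or order is lost, and the result is not on the same target as the correlations. That conclusion does not depend on how many classes are used.

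The size does. For a roughly normal score cut in two between 50/50 and 80/20, about 36% to 51% of the linear information is lost, against 21% with three equal classes and 10% with five. The two-class cut is an assumption; the individual thresholds under RQII make it plausible but do not establish it for RQI.

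The main RQI correlations are not affected. The study is exploratory, so no error rate, sample size or confirmatory result changes.

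**What to change.** In the RQI paragraph of section 1.6, replace the classifier by *a Random Forest regression on the PHQ-2 and PHQ-9 scores*, and take the Kernel SHAP ranking from that model. State that it is validated with the schemes already described in the same section: leave-one-subject-out for models on all participants, and time-series cross-validation for within-subject models. Keep classification of high-severity days as a secondary analysis, with its classes defined.

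The cost is a little extra analysis work. Last patient out was in December 2024 (section 1.3.3), and the change needs no new data because the scores were recorded in graded form.

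### USEM/GIMME is named as the validation of the RQI person-specific findings, but it is refitted to the same days, so it checks model form and lag structure, not chance

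*Protocol article*

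**What the plan says.** Section 1.6 (Data analysis) of the protocol article answers RQI in four steps.

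- **Pooled analysis:** "we will conduct multilevel correlations between depressive symptom severity (PHQ-2, PHQ-9) and features derived from MS data through the application of data-driven methods". On the predictors it adds: "All MS features will be included in the mixed model as fixed effects".
- **Person-specific repeat:** because multilevel models pool within-person variability, "we will repeat analysis for each participant separately".
- **Non-linear model:** "a Random Forest classifier will be used to account for non-linear associations", with Kernel SHAP for feature importance.
- **Validation:** "To validate our findings on an idiographic level, we will explore the use of unified structural equation modelling", including GIMME for group-level and individual paths.

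Out-of-sample schemes come in the next part of the section, which is introduced as addressing RQII. Models on all participants get leave-one-subject-out cross-validation, and "within-subject models employ time-series cross-validation" together with a rolling scheme. The one sentence that covers both research questions concerns sensitivity analyses on the amount of input data. It does not mention a hold-out.

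Section 1.1 gives one year (365 days) per person and section 1.2 gives 15 participants, of whom 10–12 are expected to be complete. The study is declared exploratory, without confirmatory testing.

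**The concern.** Suppose a same-day correlation arises by chance in one patient's year. The same-day path in a USEM fitted to that year is estimated from the same pairs of values. The two results therefore share their sampling error, and agreement between them is not independent evidence. What the second model adds is adjustment for lags. That guards against associations created by autocorrelation alone, but not against chance in general.

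This matters because person-specific markers are the first of the two proof-of-concept aims, and the analysis screens many features in each of up to 15 people. A marker described as validated after a same-data refit would carry more weight than it has earned. The point is not that validation detail is missing from a condensed article. The article itself names what validates RQI, and the named step cannot do that job.

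**Working it through.** **1. What data can the validation step use?** The only data described are 15 participants followed for one year each. No split is stated for RQI. That USEM/GIMME uses the same days is therefore an inference, but no other source is described.

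**2. Inputs.** The document gives no significance level, feature count, autocorrelation or path threshold for RQI, so there is no figure of its own to reproduce. Taken from the document: 365 daily points, about 52 weekly points, 15 persons. Assumed: 10, 20 or 40 features (10 or 20 weekly); autocorrelation φ of 0, 0.3 or 0.6 in both series; a 5% threshold at each step.

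**3. Null simulation** (400 simulated persons per setting, no true association).

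- Flag: within-person correlation with p < 0.05.
- Same-data check, a least-squares stand-in for the symptom equation of a lag-1 USEM: y(t) = a + b·y(t−1) + c·x(t) + d·x(t−1) + e(t). A flag is confirmed if c has the same sign and p < 0.05.
- Later-block check: flag in the first two thirds of days, then test c in the last third.

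Daily data; the ranges run over the feature counts:

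| φ | Null features flagged | Flags confirmed, same days, one path at a time | Flags confirmed, same days, all features jointly | Flags confirmed, later block |
|---|---|---|---|---|
| 0 | 4.8–5.2% | 91–92% | 56–76% | 2.2–2.7% |
| 0.3 | 7.0–7.3% | 49–52% | 37–48% | 1.9–3.1% |
| 0.6 | 17.3–18.3% | 16–18% | 15–16% | 2.2–2.8% |

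A later block should confirm a chance flag with probability 0.05 / 2 = 2.5% (significant and same sign). The last column agrees.

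Weekly data (52 points): same-data confirmation is 19–78% one path at a time and 6–39% jointly, against 1.6–3.6% in the later block.

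**4. The same results as a share of all null features.** With 20 daily features and 15 persons there are 20 × 15 = 300 person-by-feature tests.

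- Same days, one path at a time: 13.1, 10.2 and 9.5 chance associations pass both steps at φ = 0, 0.3 and 0.6. As shares these are 13.1/300 = 4.4%, 10.2/300 = 3.4% and 9.5/300 = 3.2%. Over all daily settings the range is 2.8% (4.2/150) to 4.8% (28.8/600).
- Later block: 0.4 to 1.5 pass, that is 0.4/300 = 0.1% to 1.5/300 = 0.5%.

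At φ = 0.6 the same-data step reduces flags from about 18% to about 3% of null features. It removes the autocorrelation artefacts and leaves roughly what a single test at 5% would leave.

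**5. What a later block can detect** (Fisher z, 5% two-sided, autocorrelation ignored).

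- Daily, last third ≈ 365/3 ≈ 120 days. At r = 0.2, atanh(0.2) × √117 = 0.203 × 10.8 = 2.19; power ≈ Φ(2.19 − 1.96) ≈ 0.6.
- Weekly, last third ≈ 52/3 ≈ 17 points. The smallest significant |r| is 2.13/√(15 + 2.13²) ≈ 0.48. Power is about 21% at r = 0.3 (0.310 × √14 = 1.16; Φ(−0.80)) and about 54% at r = 0.5 (0.549 × √14 = 2.06; Φ(0.10)).

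**The case against.** The strongest reply is that the sentence promises little. It only explores a method, and it follows the remark that multilevel models pool across people. Its natural purpose is thus to see whether pooled results survive a person-specific model. The article uses the word validated just as loosely for RQII, where neural networks are validated against classical methods, meaning compared with them. It sets no significance rule, assesses effect sizes and declares itself exploratory. All of this stands and lowers the severity. It does not turn a refit to the same days into a validation.

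Three stronger readings are tempting, and the document does not support them.

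- *Chance markers will be published as validated.* No rule for calling a finding validated is stated. The double 5% rule above belongs to the simulation.
- *The step passes nearly all chance findings.* The figure near 90% needs zero autocorrelation in daily ratings and counts only associations already flagged. Of all null features, about 3–5% pass both steps. The simulated equation is also a stand-in: the pooled mixed model and GIMME's group-level search were not simulated, and a stricter path threshold would lower confirmation.
- *The authors treat overfitting as their main risk.* Section 2.1 lists overfitting of predictive models, and patterns tied to the collection year, as one of three limitations. A later block within the same year cannot test whether a pattern lasts beyond that year.

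It may also be said that the cross-validation sentences are worded generally and could cover the RQI Random Forest. They might, although they stand in the RQII paragraph. They would still not cover the correlations or the USEM paths.

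**Conclusion.** The point holds in a limited form. As described, USEM/GIMME is an alternative model of the same data. It is informative about lagged dependence and model form, and uninformative about whether a person-specific association arose by chance. Under the assumed inputs, the same-data step confirms flagged daily chance correlations several times to over thirty times as often as a later block does. The size depends on feature count, autocorrelation and threshold, none of which the document states. The direction is the same in every setting tried, although on weekly data with all features fitted jointly the gap can shrink to about twofold (6% against 2.3% with 20 features at φ = 0.6).

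Severity is minor to moderate: the planned analyses can stay, but the label should change and a later-block check should be added for the daily question.

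**What to change.** **Wording.** Describe USEM/GIMME in section 1.6 as a robustness check or alternative model of the same data, not as validation.

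**Daily RQIa.** Extend the within-subject time-series cross-validation already planned for RQII. For each patient, report sign and effect size with interval in later held-out blocks beside the all-days estimate. Use the word validated only for associations that replicate there. Set the block boundaries before the associations are examined.

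**Weekly RQIb.** Report later-block estimates descriptively and do not call any finding validated. About 17 points are too few for an interval-based rule, and a lag-1 equation with some 20 features could not be estimated on them at all.

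**Cost.** Analysis time and wording only. Section 1.3.3 gives last patient out as December 2, 2024, so no new data are needed. The downside is real: some true daily associations that are weak, or that change during the year, will not replicate in about 120 days. Power is about 60% at r = 0.2 before allowing for autocorrelation and missing days. Such associations should be reported as not replicated, with their all-days estimate, and not as refuted.

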In summary, patients with depressive disorders need objective markers to monitor their illness severity and reliable, valid models to predict clinically meaningful changes in the severity of their condition. This is essential as symptom presentations can vary greatly within individuals over time [34], and those with depressive disorders experience fluctuations in both positive and negative affect [35]. Objective markers could support patients in the self-management of their illness and predictive models could inform health professionals concerning treatment decisions. As phenotypes of depression vary greatly, these markers and predictive models need to be made-to-measure for each patient. Using MS, patients can unobtrusively collect enough personal data to facilitate the creation of personalized models for data analysis. To our knowledge, however, no study has shown that personalized models based on MS data can serve as objective markers of individual illness severity or forecast depression severity for individual patients. Therefore, the current study aims to achieve a proof-of-concept showing that personal MS data can (I.) monitor and (II.) predict depression severity in individual patients. To this end, adult participants with depressive disorders will collect continuous, daily data on sleep/deep rest, physical activity (locomotion, heart rate), speech features, smartphone usage (including digital communication behaviour) as well as self-reported depressive symptom severity over the course of one year using AA methods. With this data, we aim to answer the following exploratory research questions (RQ):I.a) Are personal behaviour (sleep/deep rest, physical activity, smartphone usage) and physiology (heart rate, heart rate variability, speech) during daytime (6 a.m.–6 p.m.) associated with self-reported depressed mood and anhedonia in the evening within adult patients with depressive disorders?b) Are personal behaviour (sleep/deep rest, physical activity, smartphone usage) and physiology (heart rate, heart rate variability, speech) during daytime (6 a.m.–6 p.m.) of the last 7 days associated with the weekly self-reported depression severity within adult patients with depressive disorders?II.a) Can individualized statistical models based on longitudinal data on personal behaviour (sleep/deep rest, physical activity, smartphone usage) and physiology (heart rate, heart rate variability, speech) forecast the self-reported depressed mood and anhedonia in the evening within adult patients with depressive disorders?b) Can individualized statistical models based on longitudinal data on personal behaviour (sleep/deep rest, physical activity, smartphone usage) and physiology (heart rate, heart rate variability, speech) predict the weekly self-reported depression severity within adult patients with depressive disorders?

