### Design

1.1

This exploratory study uses an observational n-of-1 design [36], involving repeated measurements of self-reported, behavioural, and physiological outcomes over the time of one year (365 days) within individuals without manipulation of variables by the investigators. The work is carried out in accordance with the World Medical Association Declaration of Helsinki [37]. Ethical approval has been granted by the Ethics Committee of the Department of Medicine at Goethe University Frankfurt, Germany (date: 24/08/2023, reference number: 2023–1309). The study protocol has been registered in the German Clinical Trials Register (reference number: DRKS00032618).

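### For next-day and next-week prediction (RQII), the VAR's FEVD and IRF can carry the same-day association that belongs to RQI, depending on an ordering the article leaves open

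*Protocol article*

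**What the plan says.** The protocol article separates two aims. RQI.a, in the research questions just before Methods, asks whether behaviour and physiology are "during daytime (6 a.m.–6 p.m.) associated with self-reported depressed mood and anhedonia in the evening". RQII, as restated in Data analysis (1.6), asks: "Can personal MS data predict the self-reported depressive symptom severity on a) the next day(s) and/or b) the next week(s".

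For RQII, section 1.6 lists deep networks, boosted ensembles, support vector machines and autoregressive models. Within the last group it concentrates on "vector autoregressive (VAR) models and their analyses using forecast error variance decomposition (FEVD) and impulse response functions (IRF) specifically for idiographic approaches". These are the only VAR read-outs it names. It gives neither a variable ordering nor a variant (orthogonalised, generalised or reduced-form). On validation it says that "within-subject models employ time-series cross-validation [62,63] and rolling back cross-validation [64" (the quote stops inside a reference).

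The daily outcome follows the daytime sensor window: "In the evenings, daily self-reported depressive symptom severity is assessed using the Patient Health Questionnaire-2". Each participant is followed "over the time of one year (365 days) within individuals". Section 1.6 also states that the study is exploratory, with no confirmatory testing.

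**The concern.** RQII concerns what earlier sensor data say about later severity. FEVD does not measure that directly. It divides the forecast error, which is the part of PHQ that the VAR failed to predict, among the shocks to each variable. At one step ahead it contains no lagged effect, only the correlation of same-period residuals and the rule for allocating it. An orthogonalised IRF then carries that same-day shock forward through PHQ's own autocorrelation, so a next-day response appears even when the lagged sensor coefficient is zero.

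Because daytime sensing comes before the evening rating, placing the sensors first is the natural ordering. Under that ordering, a patient whose sensors only mirror the same day's mood could be described as one whose depression the sensors forecast. The Discussion rests the case for timely self-management or treatment on prediction ahead of time, so the difference between a concurrent marker and a predictor matters.

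**Working it through.** The article gives no FEVD share, response size or error rate, so there is no figure to reproduce. The check asks what the named read-outs return when past sensor data add nothing beyond PHQ history.

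**Inputs from the article:** 365 days per participant; about 52 weekly values (365 / 7 = 52.1); daytime sensors before evening PHQ-2; target the next day or week.

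**Assumptions, not in the article:** a VAR(1), the autocorrelations, the number of features and the same-day residual correlation.

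**Step 1, algebra with one sensor.** Let PHQ have autocorrelation a, a zero lagged sensor effect, and a same-day innovation correlation ρ. With the sensor first, the PHQ innovation is ρu₁ + √(1−ρ²)u₂, where u₁ is the sensor shock. The sensor share at horizon h is

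ρ²·Σa²ʲ / Σa²ʲ = ρ², with j running from 0 to h−1.

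It is therefore the same at every horizon: 4%, 9%, 16% and 25% for ρ = 0.2, 0.3, 0.4 and 0.5. The raw generalised FEVD gives the same values. Normalised, it is ρ²/(1+ρ²): 3.8%, 8.3%, 13.8% and 20.0%. With PHQ first the share is 0%.

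The orthogonalised response of PHQ one day later is a·ρ. With a = 0.5 this is 0.5 × 0.3 = 0.15 or 0.5 × 0.5 = 0.25. The reduced-form response at lag 1 is zero.

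**Step 2, simulation with one sensor** (300 series of 365 days, both autocorrelations 0.5).
- Sensor-first share at 1 and 7 days: 8.8% and 9.2% at ρ = 0.3; 25.3% and 25.8% at ρ = 0.5.
- In the same data, out-of-sample squared error is about 0.4–0.5% worse with the lagged sensor than with a PHQ-only autoregression.
- Granger tests reject in 2–6% of series at the 5% level, over ρ = 0, 0.3 and 0.5.

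**Step 3, ten sensor features** (400 simulated patients per row, all autocorrelations 0.4, all lagged cross-effects zero). Mean sensor share of PHQ forecast-error variance:

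| Series | Same-day R² | Sensors first, 1 / 7 steps | PHQ first, 1 / 7 steps |
|---|---|---|---|
| 365 daily | 0 | 2.8% / 6.5% | 0% / 3.7% |
| 365 daily | 0.1 | 12.5% / 15.8% | 0% / 3.6% |
| 365 daily | 0.2 | 22.2% / 25.0% | 0% / 3.7% |
| 52 weekly | 0 | 25.7% / 44.1% | 0% / 24.4% |
| 52 weekly | 0.2 | 41.0% / 55.4% | 0% / 24.6% |

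For daily data with R² 0.2 and sensors first, the 5th to 95th percentile at seven steps is 19–32%. With five features the corresponding means are 21.0% / 22.2%, against 0% / 1.9% with PHQ first.

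Two effects are present. In daily series the same-day association dominates: 25.0 − 6.5 = 18.5 percentage points at seven steps. In weekly series most of the share is finite-sample bias: 44.1% arises with no same-day association, and R² 0.2 adds 55.4 − 44.1 = 11.3 points.

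**Step 4, does cross-validation reveal this?** In the ten-feature daily null (last 30% of days held out), the VAR beat a training-mean forecast in 92–95% of patients, through PHQ's own autocorrelation. Its squared error was nevertheless about 4% worse than that of a PHQ-only autoregression. Validating the whole VAR would look like success, and only the PHQ-only comparator shows that the sensors added nothing.

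**The case against.** Several stronger readings are tempting, and the article does not support them.

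- **That FEVD and IRF always credit same-day co-movement to the sensors.** They do so only with sensors first or a generalised variant, and only if same-day residuals are correlated. PHQ-first ordering and a reduced-form IRF avoid it. The article fixes neither, and such detail may properly sit in a fuller plan.
- **That RQII rests on FEVD and IRF.** It does not. Other model classes and time-ordered cross-validation also bear on it, and these do score forecasts on later data.
- **That every patient would be falsely labelled predictable.** An estimated non-negative share almost always exceeds zero, but nowhere does the article adopt a rule that a share above zero means prediction. It disclaims confirmatory testing, so there is no error rate to inflate.
- **That past sensor data predict nothing at all in these examples.** With autocorrelation 0.4 and same-day R² 0.2, yesterday's sensors alone explain 0.4² × 0.2 = 3.2% of today's PHQ. The null used here is no contribution beyond PHQ's own history. Prediction from sensors alone is a legitimate separate aim, given the concern about self-report burden and the planned sensitivity analysis of sensing data only.
- **That same-day prediction is outside RQII.** The introductory wording of RQII.a is to "forecast the self-reported depressed mood and anhedonia in the evening within adult patients with depressive disorders", with no next-day lag. On that wording the within-day order is defensible. The next-day target comes from section 1.6.

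These points narrow the concern but do not remove it. FEVD and IRF on their own cannot separate RQI co-movement from RQII prediction. The article names no PHQ-history-only comparator: its stated input contrast is all ambulatory data against sensing data alone.

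**Conclusion.** The concern holds in conditional form. The named read-outs can mix the same-day association into the answer to a next-day or next-week question. In daily series with ten features and same-day R² 0.2, the sensors-first share is about 22–25% when sensors add nothing beyond PHQ history, against 0% at one step and about 4% at seven with PHQ first. With R² 0.1 the sensors-first share is about 13–16%. In weekly series, seven-step shares of about 24% (PHQ first) to 44% (sensors first) arise from finite-sample bias alone.

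These sizes rest on an assumed VAR(1), autocorrelation, feature count and R², none of which the article gives. The direction follows from the algebra. This should be settled before the VAR results are interpreted, but it does not undermine the planned cross-validated comparisons.

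**What to change.** For the idiographic VAR under RQII:

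1. Compare each patient's FEVD share and IRF with a residual bootstrap in which the lagged sensor-to-PHQ coefficients are set to zero. This reference also absorbs the finite-sample bias, which PHQ-first ordering alone does not. In simulation, null patients exceeded it in 0–10% of cases, and it still detected a real lagged effect.
2. Report the VAR's cross-validated error against a PHQ-only autoregression. Describe sensors as predictive beyond PHQ history only where they exceed these references. In an exploratory study this is a descriptive yardstick, not a test.
3. Report FEVD and IRF with PHQ first as well as in the within-day order, and assign the same-day component to RQI.
4. Judge prediction from sensors alone separately, by out-of-sample error.

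The cost is some wording and modest computation, with no new data. Reported sensor contributions will be smaller. The cross-validated results already planned are unaffected.
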